### 3. Study Design

#### 3.1 Overview

The goals of the proposed study are to develop intervention strategies using mhGAP-IG and G-IPT through capacity building and implementation to address depression among pregnant and parenting adolescents. The first 1.5 Years (1-18 months) will focus on mhGAP/IPT-G strategies development to fit Kenyan MCH contexts. The 1.5-2.5 Years (19-30 months) will focus on mhGAP/IPT-G adolescent version manual development, and capacity building for mhGAP/IPT-G implementation and research. The 2.5-4 Years (31-48 months) will focus on implementing mhGAP/IPT-G model in real world MCH settings and evaluate the impacts. [Figure 1](#) shows research tasks, processes, and timeline.

This research study will be conducted based on a [partnership approach](#) that includes diverse governmental, clinical, research, and community stakeholders. We will establish an Advisory Board to facilitate cross-level partnerships and leaders-stakeholders' discussion around adolescent mental health intervention, service, and policy issues. This approach also has implications for building leadership and system capacity (e.g., through co-learning and increasing stakeholders' attention and knowledge to the gaps and developing actions toward strategy and policy development) (58).

The Advisory Board will include 13 representatives, including 3 MCH (1 leader/director, 1 nurse, 1 CHW), 2 governmental (1 MOE, 1 MOH), 2 academics (1 health service/implementation, 1 Clinical researchers), 1 advocacy (1 representative NGO leader), and 2 community stakeholders (2 caregivers of pregnant adolescent, 4 adolescent representatives). The members will meet regularly (3 times a year) throughout study years.

The eligibility criterion and terms of reference of the advisory are as follows.

For the four adolescent representatives we will seek one pregnant adolescent and one new adolescent mother and two male adolescents. The eligibility criterion would be:

- Willing to consent to participate,
- One pregnant adolescent and one new mother ages 13-16,
- Another pregnant adolescent and new mother ages 16-18,
- Willing to join the meetings held at the community center or at the health facility.

For all other stakeholders, the eligibility would be:

- Willingness to sign informed consent to participate in the study and for the deliberations to be recorded,
- Willing to engage with the issues around mental health and adolescent pregnancy,
- Willingness to commute to the health facility or community center for meetings three times a year.

The meetings may last between 2-3 hours and a minimum of 9 members need to be present for the meeting to take place.

The advisory board members would be paid transport and offered refreshments like tea, soda etc for the time they spend with the researcher and her team.

The meetings would center on:

1. understanding barriers and strategies to mitigate these barriers to mental health care in pregnant adolescents,
2. findings of the qualitative work
3. Discussing mhGAP adaptation process.

Additionally, there would be a technical advisory board. *The technical advisory board comprises of members whose organizations provided support letters during the grant and formally committed to providing technical guidance.*

Eligibility:

- Adults above 18 of years and technical persons representing mental health and health policy implementing partners in Kenya,
- willing to sign consent form for participation in the study,
- Willingness for discussion to be recorded.

The meetings would be held twice a year to discuss the key findings of the work and refine dissemination and implementation plan further. Refinement of the three implementation strategies – task-sharing/shifting, engagement with adolescents and stigma reduction would be the key focus. The technical advisory would be paid transport allowance and offered refreshments. The meetings would last 2-3 hours on days convenient for most members.

- UNFPA, [name] and [name]- responsible for sexual and reproductive health issues, working on adolescent girl child mental health
- MoH, [name] -responsible for integrating mhGAP in clinical workflow at primary care level,
- Nairobi County Health Directorate, [name], - responsible for task sharing and stigma reduction strategies to address depression.
- Nairobi County preventive health- [name]
- WHO, [name] – responsible WHO mhGAP adaptation and local capacity building in mental health
- UNICEF, Regional Office- [name] Adolescent Specialist
- WHO HQ Geneva- responsible for G-IPT adaptation and mhGAP for adolescent peripartum depression management – Drs [name] and [name]

Figure 1. Research Tasks, Processes, and Timeline

[figure not shown]

### 3.2 Study Framework

The adaptation, implementation, and evaluation of the mhGAP/IPT-G will be **guided by an integrated conceptual model** that combined two D&I frameworks, *The Consolidated Framework for Implementation Research (CFIR)* (55), which accounts for five domains of contextual factors that may influence key determinants that impact outcomes, will be used to guide Aims 1 & 2 studies. A rigorous mixed methods study will be used to study strategies to adapt and improve fit of mhGAP-IG and IPT-G for Kenyan adolescent population and MCH implementation contexts. *The Conceptual model of Implementation Outcomes* (56) which provides conceptual constructs for guiding implementation, service, and effectiveness outcome assessments, will be applied to guide the evaluation of implementation-effectiveness study (Aim 3). Figure 2 shows our integrated conceptual model for the proposed study.

[figure not shown]

Figure 2. Integrated Conceptual Model for the Study

Figure 3: Timeline

[figure not shown]

### 3.3 Methodology for Aim1

(Study barriers and strategies to improve mhGAP-IG/IPT-G fit and implementation).

To understand ‘fit’ of the mhGAP/IPT-G and study multi-level barriers/strategies to promote utilization and impacts of IPT-G and mhGAP, we will carry out a mixed methods study, including qualitative and quantitative data collection. Quantitative data collection will focus on D&I readiness contexts and new D&I tools pilot testing, which will be used for Aim 3 evaluation study.

**Data Collection Focus and Procedures:** We will conduct 8 focus groups (n=40) with representative diverse stakeholders (i.e., including 2 groups for pregnant adolescents and new adolescent mothers, 2 groups for adolescent caregivers and partners, 2 groups for MCH staff, 1 group for community advocates and policy leaders, and 1 group for child and adolescent mental health professionals). Each focus group discussion (FGD) will have about 5 participants. Each group will participate in three FGD meetings. One meeting will focus on barriers/strategies related to mhGAP-IG, and the other meeting will focus on barriers/strategies related to IPT-G. The third FGD would be focusing on mental health treatment preferences of pregnant adolescents. Each focus group will last 1½ to 2 hours. Participants will participate in a FGD and complete a survey, and these will be carried out in English or Kiswahili (as English is the official language in Kenya). Focus group guides/questions and quantitative survey will be adapted from existing D&I studies (57), or existing D&I measures (see measures under Aim 1). Stakeholders’ views on barriers and strategies in 5 CFIR domains (see Figure 2 second left box) will be discussed separately for mhGAP and IPT-G. Informed by our previous need assessment work, strategies related to livelihood problem, partner/family engagement, knowledge gap, and stigma reduction will also be explored.

- For focus group with *adolescents and families/partners* (n=20, recruited through 2 MCH clinics that we have partnership with from previous MCH epidemiological studies), discussion will focus on CFIR individual, intervention, and inner setting domains, and examine their knowledge related to perinatal depression, and views (including barriers and potent

ial strategies) related to adolescent pregnancy, mhGAP/IPT-G (fit, usefulness, perceived feasibility and effectiveness of IPT-full and mini versions), family member/partner engagement, support, and empowerment strategies, and preference for integrated mental health-MCH services. See appendix.

- *For the MCH providers/staff and mental health professionals (n=15, recruited through 2 MCH clinics [same as the sites for family recruitment] and mental health professional networks)*, discussion will focus on the CFIR inner setting, individual/staff, intervention, and process domains. We will examine fit, barriers, and implementation strategies for mhGAP and IPT-G implementation in MCH settings (e.g., collaborators' roles, task-shifting/sharing strategies, workflow logistic/coordination strategies), staff attitude/belief toward EBI practices, perceive effectiveness, and MCH implementation climate. See appendix.
- *For the community advocates and policy stakeholders (n=5, recruited through Ministry of Health and NGO networks)*, discussion will focus on the CFIR intervention, process and outer setting domains, and examine barriers and strategies related to mhGAP and IPT-G. In addition, community awareness/public educational and stigma reduction strategies (outer setting strategies) will be explored to facilitate community support to address adolescent pregnancy and maternal mental health needs, which also has implications for public health impact promotion (58, 59). See appendix.

**To better identify mhGAP/IPT-G workflow barriers and strategies in MCH contexts**, MCH site visits and workflow observation will be arranged for the Community and Technical Advisory Board members (n=18, including researcher). The observation will focus on MCH structure and perinatal service workflow. This will allow the Board and research members to gain better understanding about the clinical setup, implementation barriers and strategies, which will facilitate better and more sustainable workflow plan/strategy development to support mhGAP/IPT-G implementation. To ensure confidentiality, informed consent for all participants will be obtained prior to the data collection. Participating provider personnel and family members will be compensated for their time. Participating mental health professionals and officers of NGO/ Ministry of Education/ Ministry of Health will also be compensated.

Creating an adapted G-IPT model for pregnant adolescents in Kenya requires (1) in-depth qualitative analysis of depression care needs from multiple stakeholders; (2) analysis of needs and incorporation of these needs into a treatment manual for this group. Conjoint Analysis has been used in marketing research, but it has evolved as a robust device to measure healthcare preferences of patients. Grounded in economic theory, conjoint analysis assumes that clients make choices among products or services by considering characteristics or attributes—for example, size, color or brand or home or clinic-based care—and making tradeoffs among these attributes to arrive at a final choice. In conjoint analysis used for healthcare, clients are presented with hypothetical

Service scenarios with varying combinations of attributes and are asked to choose among these scenarios. Conjoint analysis (CA) and mixed methods such as Q-methodology, Principle Coordinate analyses enable us to estimate relative preference weights and their corresponding trade-offs when it comes to treatment preferences and engagement stances (38). Patients' preferences are particularly salient in depression treatment, because multiple efficacious treatments (for example, combination of antidepressants and psychotherapies) and modalities (for example, group and individual) or different types of psychotherapies (cognitive-behavioral or relational like IPT) exist.

Knowing what these young women would consider beneficial and ways to bolster an evidence based and well-accepted group interpersonal psychotherapy for this age group is the key motivation for this study. Conjoint analysis involves defining of lived experience of depression during pregnancy, preferred intervention for depression, barrier-to-care, stigma in seeking mental health care attributes, attribute levels to the above-mentioned themes will be assigned (treatment delivered at home or clinic, depression care by peer or health worker etc and create hypothetical scenarios. Clinical guidelines like WHO's mhGAP, Kenyan National maternal and child health and mental health policies along with formative qualitative work will guide the process. For the secondary aim of addressing adolescent mental health treatment preferences, the following methodology would be adopted.

**Target Population:** Pregnant adolescents in Kariobangi and Kangemi informal settlements visiting the MCH and Pumwani Maternity hospital as a referral. Through initial contact with these women we will use snowballing technique to reach others who have poorer community support and health facility interaction, a subset of health workers from the facility, community health workers, school teachers and caregivers.

**Recruitment:** Direct approach of soliciting participation from those in these facilities and associated with the facilities.

**Inclusion Criteria:**

- Seeking primary care at the center;
- ages 13-18 years;
- ability to give informed consent;
- availability for duration of interview
- intact cognitive functioning

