**Exclusion Criteria:**

Women over 18 years of age, and unable to give informed consent.

**Enrollment (N=157) and Study Procedures:** Using a simple conjoint experimental task, key preferences will be elicited to address the barriers identified above. Multidimensional scaling and will create a list of closed choice scenarios.

**Sample Size:** Total sample size of 157 young women will be given a short conjoint survey. Sample size considerations will be based on the standard formula for sample size estimation for discrete

choice experiment analysis published by Johnson and Orme. In which, the rule of thumb as proposed by Johnson and Orme (60, 61) suggests that the sample size required for the main effects depends on the number of choice tasks (t), the number of alternatives (a), and the number of analysis cells (c) according to the following equation:  $N > 500c/(t*a)$ , indicating that a minimum sample size of 94 respondents was needed to all two-way interactions. As this rule of thumb is sometimes insufficient, and to allow for sub-group analyses, we will then increase the sample size by 40%, resulting in a targeted sample size of 157 respondents(62).

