#### Data collection procedure

##### *Pre-testing phase*

The goals of this phase are to ensure appropriate adaptation of mental health measures for population-level measurement. This will be achieved through translation/adaptation and back-translation, qualitative data collection and analysis using focus groups and interviews.

Additional objectives of the research activities conducted in the initial phase are to gain an in-depth understanding of knowledge and beliefs surrounding adolescent mental health, including causal attributions, risks to mental and emotional well-being in everyday life, and help seeking. Culturally grounded elements of mental health, care and support, and of stigma will be explored. The qualitative data contributes independently to our understanding of culturally salient concepts of mental ill-health, and will improve the quality of the survey measures and ability of mental health interventions to best cater to the needs of adolescents.

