## I. Questionnaire administration and validation phase

### *Questionnaire Administration (STEP 6)*

Survey questionnaires will be administered to 250 adolescents and 100 parents of younger adolescents. Surveys may be administered within the school context or at home, depending on school-year and feasibility assessment of the setting. The questionnaire will be administered by research assistants using manually the entire tool, including all optional test modules, is anticipated to take 30 minutes or less to administer. As part of this work all research assistants will receive basic tool administration training and be fluent in English.

A preliminary draft of the measures (instruments) planned for inclusion in the survey is provided in the Appendix 44-55. The final revisions of tools will be informed by the qualitative data results. Cards with written response options may be made be available to all respondents. Specific images and response items on the cards will have been previously validated during the focus groups and cognitive interviews. A selection of 50 participants will be asked to complete the questionnaire a second time, 1-2 weeks following the initial administration – to allow for test-retest analysis of the stability of the measures.

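### The conjoint study's care-seeking criterion makes no exception for the low-contact girls it snowballs to reach, and the same line fits poorly with the general sample described for the tool validation

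*Protocol*

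**What the plan says.** **Conjoint study (protocol section 3.3).** The target population opens with "Pregnant adolescents in Kariobangi and Kangemi informal settlements visiting the MCH and Pumwani Maternity hospital as a referral". The next sentence goes wider: "we will use snowballing technique to reach others who have poorer community support and health facility interaction". Recruitment is described as "Direct approach of soliciting participation from those in these facilities and associated with the facilities". The inclusion list then starts with "Seeking primary care at the center" and continues with age 13-18, consent, availability and cognition. It carries no exception for girls found by snowball and does not mention pregnancy, which appears only in objective 1.3 and the target population.

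**Tool validation (section 3.3, inclusion criteria for adolescents).** The same five lines are repeated with the age range changed to 10-19. Objective 1.4 in section 2.2 describes a general adolescent sample together with pregnant adolescents, and the Synopsis lists 250 adolescents separately from 50 pregnant ones. The Pre-testing phase aims to "ensure appropriate adaptation of mental health measures for population-level measurement". Step 6 says "Surveys may be administered within the school context or at home", depending on the school year and feasibility. Step 7 calls back people scoring above the cut-off, and healthy controls, for a diagnostic interview.

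**The concern.** In the conjoint study the recruitment text and the eligibility rule pull in opposite directions. A recruiter who follows the snowball and then applies the inclusion list has to turn away any girl who is not seeking care at the centre, and those are among the girls the snowball is meant to find.

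This matters because the selection variable is tied to what is measured. Treatment setting is one of the example attributes in Table 1, with the maternal and child health facility, the home and a community centre as its levels. The results feed the Aim 2 adaptation. Girls who already use the facility may well weigh that attribute differently from girls who seldom do. A larger sample of facility users would not correct this, and no analysis can recover girls who were never enrolled.

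In the validation study the question is which population the cut-offs, sensitivity and specificity describe. If all respondents are care-seekers, the results describe care-seekers. The section on the relevance of the work, by contrast, looks ahead to later national data collection.

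**Working it through.** This is a comparison of texts. The point disputes no figure.

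**Conjoint study**

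1. People to be reached: girls visiting the facility, plus others found through "snowballing technique to reach others who have poorer community support and health facility interaction".
2. People admitted: only those seeking primary care at the centre.
3. Overlap: a snowballed girl who attends irregularly can satisfy both. A snowballed girl who is not seeking care there satisfies the first and fails the second.
4. The criterion therefore removes part of the snowball's yield, and removes it by facility use, the characteristic the snowball was chosen to vary.

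**What the sample size can tell us.** The plan states a minimum of 94, then "we will then increase the sample size by 40%, resulting in a targeted sample size of 157 respondents". The total reproduces as 94 / (1 - 0.40) = 156.7, rounded up to 157. Multiplying instead gives 94 x 1.40 = 131.6, or 132. The total is not at issue here. As an assumption only, suppose a share f of 157 recruited girls were not seeking care at the centre and were not replaced:

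- f = 10%: 157 x 0.90 = 141.3, so 141 stay eligible.
- f = 40%: 157 x 0.60 = 94.2, so 94 stay eligible, equal to the stated minimum.
- f = 50%: 157 x 0.50 = 78.5, so 78 stay eligible.

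The protocol gives no value for f. If rejected girls are replaced by attenders, the count stays at 157 and only the composition changes. The issue is therefore who is in the sample, more than how many.

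**Tool validation**

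| Element | Points to |
|---|---|
| Objective 1.4, general adolescent sample | wider than care-seekers |
| Pre-testing goal, population-level measurement | wider than care-seekers |
| Step 6, school or home as possible survey settings | compatible with both |
| Appendix 18, a consent form for students aged 18-19, listed between an assent form and a caregiver consent for ages 10-17 | wider than care-seekers, by inference |
| Objective 1.4, tools for use in primary care | care-seekers |
| Section 3.3, testing at the study sites | care-seekers |
| Inclusion list | care-seekers only |

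The document supports two source populations and does not choose between them.

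**The case against.** The strongest reply on the conjoint study is that the main target population is girls visiting the facility, which agrees with the criterion. The snowball also seeks girls with poorer facility contact, which is not the same as none. The snowball sentence further names health workers, teachers and caregivers, who cannot be among the 157 young women, so that sentence covers more than the conjoint respondents. All of this is fair. It means the criterion does not shut out every low-contact girl. It does not supply an exception for those who are not seeking care at the centre.

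On the validation study the reply is stronger. Step 6 is optional and concerns where the survey is given, not who is sampled, and a care-seeking adolescent can be surveyed at school. The tools are tied to primary care and to the study sites. The healthy controls are called back from people already surveyed, so healthy means without the condition, not a non-patient. A reader might infer that the validation requires a school or home sample, or that all 250 respondents could be ineligible. The document says neither: no passage states that any of the 250 are non-attenders. What remains is an unresolved mismatch with the general-sample and population-level wording.

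It is also fair to say that this is formative work. Aim 3 has its own criteria, including willingness to attend group sessions at the clinic, and no trial outcome or power figure changes. The omission of pregnancy from the inclusion list is minor, since the objective and the target population both state it.

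**Conclusion.** The contradiction in the conjoint study stands: the plan sends recruiters to girls with weak facility contact and then admits only those seeking care at the centre. The resulting tilt toward facility users bears directly on the treatment-setting attribute. The validation study has a real but softer inconsistency about its source population, which needs to be reconciled.

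No size of bias can be given. A reader might be tempted to state a shift in percentage points, but that needs the share of girls outside care and their preferences, and the protocol gives neither. The planned analysis also estimates relative utilities, not shares of girls preferring each setting. Nor does the point cover all quantitative work in Aim 1, because section 3.3 also includes a stakeholder survey on implementation readiness. The conclusion assumes only that the inclusion lists will be applied as written. It is worth correcting before recruitment, because eligibility cannot be repaired at analysis.

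**What to change.** **Conjoint study.** Replace the first inclusion line with: currently pregnant, and either attending the study facility or reached through the snowball contact. Keep the other lines. Record the recruitment route for each participant and report preferences by route as well as overall. The sample was already enlarged partly to allow subgroup analyses, so this suits the existing plan. A snowball without quotas will not mirror population proportions, so results by route should be described as such and not pooled into a population share.

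**Tool validation.** Choose one of two courses. Either widen the criterion to adolescents aged 10-19 recruited through the study-site clinics, schools or homes, with the route recorded, or keep the criterion and limit the stated target population and the conclusions to care-seekers. In both cases, select the healthy controls for the diagnostic interview from the same surveyed sample as the cases. Taking controls from one recruitment route only would confound diagnosis with source and could distort specificity and the area under the curve.

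**Cost.** Two eligibility lines and one data field, with no added participants. The downside is a slightly smaller facility-attender subgroup within the 157 and, if the validation criterion is widened, fewer care-seekers among the 250.
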